### Statistical Analysis

2.14

Statistical analysis will be performed using the most recent version of SPSS (IBM Corp., Armonk, NY, USA) available at the time of analysis. Analysis will adhere to the intention‐to‐treat principle for all randomised participants. Standard tests to assess continuous data for normal distribution will be used and transformation carried out if required. The primary outcome will be averaged data from 5 questions from the MOSQ [13]. Analysis will be performed using a repeated measures analysis of variance. Four effects are worthy of consideration: (i) the treatment effect, (ii) the order effect, (iii) the treatment‐order interaction effect and (iv) the carry‐over effect [46]. The treatment effect is the direct effect of minimalist versus balance‐enhancing shoes. The order effect implies that the sequence in which treatments are given influences the outcome. The treatment‐order interaction effect implies that the effect of the treatment is influenced by the order in which it is presented. Finally, the carry‐over effect refers to the effect of the previous treatment on the next treatment. In our study, we consider the carry‐over effect to be negligible, as the outcome measures are specific to the shoe being worn. Multiple imputation will be used to replace any missing data using 5 iterations, with baseline scores and order as predictors. Frequency of adverse events will be compared using relative risk and risk difference statistics.

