### Outcome Measures

2.8

The primary outcome measure is footwear acceptability [13], which will be measured using a modified Monitor Orthopaedic Shoes Questionnaire (MOSQ) at weeks 6 and 12, which allows participants to have 6 weeks in each shoe condition. The MOSQ consists of seven items which address attractiveness to self, attractiveness to others, comfort, fit, ease of donning and doffing, weight satisfaction and perceived durability. All items are scored on a 100‐point VAS. Each of the 7 MOSQ items will be reported separately, but our primary outcome will be calculated from the average score of the 7 items (attractiveness to self, attractiveness to others, comfort, fit, ease of donning and doffing, weight and durability).

Secondary outcome measures will be perceived risk of falling using the Falls Efficacy Scale International (FES‐I) [34] and balance performance (upper body stability when walking, using the validated GyKo sensor) [35, 36], both measured at weeks 6 and 12. The FES‐I is a widely accepted tool to assess an individual's concern about falling [37], which asks about 16 activities and uses a 4‐point Likert scale with the following options: not at all concerned, somewhat concerned, fairly concerned and very concerned. The minimum score is 16 (no concern about falling) and the maximum score is 64 (severe concern about falling). Both the MOSQ and FES‐I will be administered as surveys using REDCap.

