### Sample Size

2.13

In crossover trials, each participant acts as their own control, which greatly reduces between‐participant variability and therefore reduces the required sample size. In the absence of a widely used primary outcome measure, we averaged data from five questions from the MOSQ [13] used in our recent pilot study [11]. These questions are related to participant perceptions of the attractiveness (to both self and others), comfort, fit and ease of donning and doffing of minimalist shoes versus balance‐enhancing shoes, scored on a 0 to 100 visual analogue scale. Using the crossover trial formula described by Jones and Kenward [44], a mean difference of 12.5, standard deviation of 27.8, power of 0.80 and alpha level of 0.05, we determined that a total of 39 participants would be required. This equates to an effect size of 0.45, which is considered a medium effect size using the thresholds proposed by Sawilowsky [45]. Our key secondary outcome measure, the FES‐I [34], has a mean difference of 8.0, and standard deviation of 15.6 when comparing participants with a low and high concern about falling. Using the same formula, we determined that a total of 30 participants would be required, which equates to a medium effect size of 0.51 [45]. To account for an estimated 10% attrition rate, we will recruit an additional 5 participants. Therefore, we will recruit 44 participants to address the sample size requirements for both our primary and key secondary outcome measures.

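### The protocol defines the primary outcome as a seven-item MOSQ average in Outcome Measures but a five-item average in Statistical Analysis, and gives no planning figures for the seven-item version

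*Protocol article*

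**What the plan says.** Three sections of the protocol article bear on the primary outcome.

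- **2.8 Outcome Measures:** "our primary outcome will be calculated from the average score of the 7 items". The seven are attractiveness to self, attractiveness to others, comfort, fit, donning and doffing, weight and durability. Each item is also to be reported separately.
- **2.14 Statistical Analysis:** "The primary outcome will be averaged data from 5 questions from the MOSQ". The five are not named there.
- **2.13 Sample Size:** "we averaged data from five questions from the MOSQ", taken from the pilot study. These are described as "attractiveness (to both self and others), comfort, fit and ease of donning and doffing of minimalist shoes" against balance-enhancing shoes, so weight and durability are left out. The inputs are "a mean difference of 12.5, standard deviation of 27.8, power of 0.80 and alpha level of 0.05", and the result is "we determined that a total of 39 participants would be required".

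The Abstract names only a modified MOSQ, with no item count, so it does not settle the matter. No section says which definition governs, calls the five-item score a proxy, or gives planning figures for the seven-item mean.

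**The concern.** Sections 2.8 and 2.14 each say what the primary outcome is, and they cannot both hold. This is not detail left to a separate analysis plan: whoever writes that plan would find support in the protocol for either version. Both averages can be computed from the data to be collected, and section 3.1 says recruitment has begun. Until one is fixed, the choice could be made after results are known.

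The choice could matter. Weight and durability carry two sevenths of the seven-item score, and the documents give some reason to think the shoes could be rated differently on both. Section 2.6 gives 191–258 g for the minimalist shoe and 328–430 g for the balance-enhancing shoe. The Background says minimalist shoes tend to be less durable. The first might favour the minimalist shoe and the second the balance-enhancing shoe.

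The power statement is a second, smaller matter. It was derived for the five-item score, while the Discussion presents the trial as appropriately powered for acceptability without saying which score is meant.

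**Working it through.** **Step 1. Reproduce the stated figure.** Inputs from 2.13: difference 12.5, "standard deviation of 27.8", power 0.80, "alpha level of 0.05". The type of SD and the sidedness of alpha are not stated. Reading the SD as that of within-participant differences and alpha as two-sided:

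N = (1.960 + 0.842)² × (27.8/12.5)² = 38.8, rounded up to 39.

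The standardised difference is 12.5/27.8 = 0.45, as stated. Normal-approximation power at 39 is 80.2%. The arithmetic is sound for the five-item score.

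**Step 2. Relate the two averages.** Let x be the mean between-shoe difference on weight and durability taken together, signed so that positive means the same direction as the 12.5 points. Then

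seven-item difference = (5 × 12.5 + 2x)/7 = (62.5 + 2x)/7.

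- x = 12.5: (62.5 + 25)/7 = 12.5
- x = 0: 62.5/7 = 8.93

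The case x = 0 covers both no difference on either added item and equal differences that cancel.

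**Step 3. Power for the seven-item mean with 39 completers.** The normal approximation is used so that results compare directly with the stated 80%: power = Φ(difference/SD × √39 − 1.960). Neither x nor the seven-item SD is in the documents. The values below are assumptions, with SDs either side of 27.8 to show the range.

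| x (assumed) | Seven-item difference | Power, SD 24 | Power, SD 27.8 | Power, SD 32 | N for 80% at SD 27.8 |
|---|---|---|---|---|---|
| 25 | 16.07 | 99% | 95% | 88% | 24 |
| 12.5 | 12.50 | 90% | 80% | 68% | 39 |
| 6.25 | 10.71 | 80% | 67% | 55% | 53 |
| 0 | 8.93 | 64% | 52% | 41% | 77 |

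Worked case, x = 0 and SD 27.8: 8.93/27.8 × √39 = 2.006; 2.006 − 1.960 = 0.046; Φ(0.046) = 0.52.

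**Step 4. Check the method.** With a noncentral t distribution on 37 degrees of freedom, the 12.5-point case gives 78% and the 8.93-point case 50%. The contrast between them is much the same on either basis.

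**Step 5. When would 80% carry over?** Only if the seven-item standardised difference is also about 0.45. With x = 0 that needs an SD near 8.93/0.45 = 19.8. The protocol does not show whether this holds.

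**The case against.** The best defence is that section 2.13 does not define the outcome at all. It says that no widely used measure existed and that five available pilot questions were averaged for planning. Sizing a trial on the items available is ordinary practice. That stands: the definitional conflict is between 2.8 and 2.14, and the power point would be met by one sentence calling the pilot score a proxy.

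It can also be said that selective reporting is partly limited. All seven items will be reported separately, so both mean differences could be recovered, though not their standard errors. Section 2.2 says the biostatistician is blinded. These points reduce the risk but do not tell the biostatistician which average to analyse.

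Three stronger readings are tempting, and the documents do not support them.

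- A reader might infer that weight and durability are the items on which the shoes will differ most. No section says so. Weights in grams are not satisfaction ratings, and the durability item is about perception. The shared items may differ too: the Discussion raises aesthetics for both shoes, and a high-collared boot with laces and Velcro may differ from a laced canvas shoe in donning and doffing.
- A reader might move both added items by 20 points in the same direction and obtain a very wide power range. Nothing anchors 20 points, and the evidence on weight and durability points in opposite directions. Section 2.13 also does not say which shoe the 12.5 points favour, so neither item can be signed against it.
- A reader might conclude that the seven-item outcome is underpowered. That is not shown; several cells in the table are at or above 80%.

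**Conclusion.** The contradiction between 2.8 and 2.14 is real, sits in current text and must be corrected, because it leaves the primary outcome open between two scores that can give different effects.

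The stated 39 participants and 80% power are correct for the five-item pilot score. For the seven-item mean the power is undetermined, not shown to be low. With SD held at 27.8 and 39 completers it is about 80% if the added items also differ by 12.5 points in the same direction, and about 52% if they show no net difference. Those figures rest on a two-sided 5% test, on 27.8 being the SD of within-participant differences, and on assumed values for the added items and the seven-item SD.

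**What to change.** Before any outcome data are examined:

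1. In 2.14, replace the five-question sentence with the average of the seven items listed in 2.8, which is the fuller and more explicit definition. Name the five-item average, with its items listed, as a sensitivity analysis.
2. In 2.13, state that 39 participants and 80% power refer to the five-item pilot score used as a planning proxy. Add that power for the seven-item mean depends on stated assumptions, and give a short range such as the one above.
3. Check that the registry entry gives the same definition. Its content cannot be judged from the protocol article.

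The cost is one sentence in 2.14, one or two in 2.13, and a registry check. No further data or participants are needed.

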### Design

2.2

This study (BALANCER‐OUT: BALAnce eNhanCing shoEs for oldeR women: OUTdoor) is a randomised crossover trial which will take place over a 12‐week period (each intervention period will be 6 weeks). Participants will be provided with both shoe types (minimalist and balance‐enhancing) with the order of wear randomised (participant intervention order will be AB or BA). Crossover to the alternate shoe condition will take place at the end of week 6. Although commonly used in crossover trials, we have deemed that a wash‐out period is not required in this trial as we have determined that any carry‐over effect would be minimal, and the outcome measures are specific to the intervention(s) being applied (i.e., we are examining the acceptability of the footwear as the primary outcome). Our approach is supported by a recent crossover trial comparing two types of shoes for older people with foot pain that did not employ a wash‐out period between interventions [12]. Figure 1 depicts the trial profile and the timing of enrolment, interventions and assessments are shown in Table 1. The study design and nature of the interventions preclude participants and researchers administering the intervention from being blinded to group allocation. However, trial personnel entering participant‐reported data and the biostatistician performing the statistical analyses for the trial will be blinded. Assessments will be performed at the Foot and Ankle Laboratory at La Trobe University, Bundoora (Victoria, Australia).

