### Randomisation

2.5

The order of the interventions (minimalist vs. balance‐enhancing shoes) will be randomised (i.e., AB or BA) using an online randomisation service (www.sealedenvelope.com). A third‐party individual who is not involved in the study design, recruitment and data analysis will create and upload the allocation sequence to REDCap. REDCap's randomisation feature allows for allocation concealment by enabling different user rights. Assessors involved in recruitment and data collection will not have user rights to access the uploaded allocation sequence. All baseline assessments will be completed prior to intervention order allocation.

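### In this AB/BA crossover the treatment-by-order interaction is the period effect, but the plan defines it as the shoe effect depending on order; order and carry-over are also listed as two effects although they are one contrast

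*Protocol article*

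**What the plan says.** The Design section sets up a two-period crossover without wash-out, in which "participant intervention order will be AB or BA". The Randomisation section uses order in the same sense: it "will be randomised (i.e., AB or BA) using an online randomisation service". The Outcome Measures section has the primary questionnaire completed "at weeks 6 and 12, which allows participants to have 6 weeks in each shoe condition", so each participant contributes one post-treatment value per shoe.

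Under Statistical Analysis, "Analysis will be performed using a repeated measures analysis of variance". The section then lists four effects as deserving attention: treatment, order, treatment-order interaction and carry-over. It defines them in turn. On order: "The order effect implies that the sequence in which treatments are given influences the outcome". On the interaction: the "interaction effect implies that the effect of the treatment is influenced by the order in which it is presented". Carry-over is defined separately, as the effect of one treatment on the next, and is taken to be negligible. No period effect is named.

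**The concern.** The definition of the interaction is a rule for reading a result, and for this design the rule is wrong. Ratings at week 12 may differ from those at week 6 for reasons unrelated to which shoe came first, such as weather for an outdoor shoe, loss of novelty, or repeating the questionnaire. That is an ordinary period effect. It is a nuisance in a crossover and says nothing about effect modification. Under the plan's definition it would be published as a finding that the acceptability difference between shoes depends on the order of wear.

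The second problem concerns order and carry-over. If they are the same contrast, the plan considers a term while also assuming that what the term measures is negligible. A reader following the text would not recognise a notable order effect as bearing on the decision to omit a wash-out.

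**Working it through.** **Inputs.** Two sequences (Design, Randomisation). One primary outcome value at week 6 and one at week 12 (Outcome Measures). Mean difference 12.5, SD 27.8, power 0.80, alpha 0.05, 39 participants before attrition (Sample Size). Assumed, because the article gives no figure: two-sided alpha, the size of any period shift, and for one check a between-participant SD of 15.

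**Which SD is 27.8?** The plan's own figure settles this. Reading 27.8 as the SD of the within-participant difference, N = ((1.960 + 0.842) × 27.8 / 12.5)² = 38.8, so 39. Then 39 / 0.90 = 43.3, so 44. Both reproduce. The SD of differences is therefore 27.8.

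**Aliasing.** Take the four cell means in the order AB period 1, AB period 2, BA period 1, BA period 2, with shoe A coded +1.

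| Contrast | AB-1 | AB-2 | BA-1 | BA-2 |
|---|---|---|---|---|
| Treatment T | 1 | −1 | −1 | 1 |
| Period P | −1 | 1 | −1 | 1 |
| Sequence S | 1 | 1 | −1 | −1 |
| T × S | 1 | −1 | 1 | −1 |
| T × P | −1 | −1 | 1 | 1 |
| Carry-over C | 0 | 1 | 0 | −1 |

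- T × S = −P in every cell: the treatment-by-order interaction is the period effect.
- T × P = −S: the order main effect is the treatment-by-period contrast.
- C = 0.5 S − 0.5 T: once treatment is in the model, differential carry-over and order are the same contrast.
- The columns mean, T, S and T × S have rank 4; adding C leaves the rank at 4.

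**What the interaction tests.** Let τ be the shoe effect, the same in everyone, and π1, π2 the period means, with no carry-over.

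E(A − B | AB) = τ + (π1 − π2)

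E(A − B | BA) = τ − (π1 − π2)

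The difference between sequences is 2(π1 − π2); τ cancels. With τ = 12.5 and a 5-point shift the two expectations are 17.5 and 7.5. The interaction contrast is 10, with no effect modification present. The average of the two is still 12.5.

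**How often it would be significant.** With 39 completers split about evenly, SE = 27.8 × √(2/19.5) = 8.90, on 37 df. From the noncentral t distribution:

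| Assumed period shift | Contrast / SE | Probability significant at 5% |
|---|---|---|
| 3 | 6 / 8.90 = 0.67 | 10% |
| 5 | 10 / 8.90 = 1.12 | 19% |
| 8 | 16 / 8.90 = 1.80 | 42% |
| 10 | 20 / 8.90 = 2.25 | 59% |

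**Simulation check** (40 participants, 4,000 runs, shoe effect 12.5 for everyone).
- No period or carry-over effect: the interaction rejects in 4.5% of runs and order in 5.1%.
- Period shift of 10: the interaction rejects in 60%, order stays at 5.2%, and the treatment estimate stays at 12.5.
- Differential carry-over of 10: the interaction stays at 5.1% and order rejects in only 13%, while the treatment estimate falls to 7.4. The expected value is 12.5 − 10/2 = 7.5.

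The 13% depends on the assumed between-participant SD of 15. With that value the within-participant sum has SD √(4 × 15² + 27.8²) = 40.9 and the contrast has SE 40.9 × √(2/20) = 12.9, so a 10-point difference is under one standard error.

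**The case against.** Several points on the other side are sound.

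- **Four effects, three estimable.** A reader might infer that the plan fits a model it cannot estimate. The text does not support that. It offers the four effects for consideration, does not promise four tests, and sets carry-over aside as negligible. Three estimable terms remain.
- **The primary comparison.** A reader might infer that the treatment result is biased. With shoe within and order between participants, the interaction absorbs the period effect, so the treatment contrast is already adjusted for it. A model labelled treatment, period and sequence is the same model under other names.
- **Consequences.** A reader might expect separate shoe effects by order, or a preliminary test that decides the analysis. The article plans neither.
- **Size.** No period effect is given anywhere, and 10 points is 80% of the 12.5-point target difference. At 3 points the excess over the nominal 5% is modest. The Discussion says that recruitment and data collection avoid December and January, which reduces seasonal change between periods but does not remove it.
- **Order and carry-over.** A significant order effect would not refute the negligible carry-over assumption by itself, because it also reflects chance differences between the two sequence groups.
- **Meaning of order.** The article does not state the factor layout, and order could be read as position, first or second. Then order would be the period effect, and the effect-modification wording would fit treatment-by-period. But that term is the carry-over contrast, so an overlap remains. The section's own definition of order, through the sequence of treatments, and the AB/BA usage elsewhere favour the reading taken here.

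None of this rescues the stated definition of the interaction, or the listing of order and carry-over as distinct.

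**Conclusion.** The point holds as an error of stated interpretation. With order meaning sequence, the treatment-by-order term is exactly the period effect and cannot show that the shoe effect depends on order in any other sense. Order and carry-over are the same contrast after treatment, so the order term bears on the negligible carry-over assumption, though with low power and mixed with chance differences between groups.

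The harm is a false secondary conclusion on the primary outcome. Its probability is about 10%, 19% and 59% for assumed period shifts of 3, 5 and 10 points, against 5% with no shift. These figures rest on 39 completers split about evenly, 27.8 as the SD of differences, two-sided 5% testing, and no carry-over.

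It does not follow that the treatment estimate, its test or the sample size is wrong. All three stand if order is the between-participant factor and carry-over is nil. It should be fixed, but the primary comparison does not depend on it.

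**What to change.** Rewrite the part of the Statistical Analysis section that defines the four effects:

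- Name three effects: treatment; period, which equals treatment-by-sequence; and sequence, which is aliased with differential carry-over and with treatment-by-period.
- Report period as a nuisance effect.
- State that the treatment-by-order term will not be read as the shoe effect depending on order.
- Say that the sequence term is the one that bears on the negligible carry-over assumption, that it has low power, and that it also reflects chance differences between the sequence groups.

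The cost is the rewording of one paragraph. Data, software, sample size and the treatment test stay as they are. The Trial Status section says recruitment has commenced and expects results in December 2026, so the wording can be settled before the analysis.

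### Section 2.14 names baseline scores and order as imputation predictors and leaves out the participant's own score from the other period, at a small cost in precision

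*Protocol article*

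**What the plan says.** Protocol article, section 2.14 (Statistical Analysis), gives the missing-data method, a count and the predictors: "Multiple imputation will be used to replace any missing data using 5 iterations, with baseline scores and order as predictors". No other section adds a predictor.

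The same section fixes a within-person analysis: "Analysis will be performed using a repeated measures analysis of variance". Section 2.13 (Sample Size) justifies the small trial because "each participant acts as their own control, which greatly reduces" between-participant variability. Its inputs are "a mean difference of 12.5, standard deviation of 27.8, power of 0.80 and alpha level of 0.05", from which "we determined that a total of 39 participants would be required". On dropout it says: "To account for an estimated 10% attrition rate, we will recruit an additional 5 participants", for a total of 44.

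Section 2.8 (Outcome Measures) gives one primary score per shoe, from the "modified Monitor Orthopaedic Shoes Questionnaire (MOSQ) at weeks 6 and 12".

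**The concern.** Each participant contributes two outcome scores, one per shoe. When one is missing and the other observed, the observed one is a natural predictor: same woman, same scale. The stated model does not use it. Given baseline and order, the imputed score is then independent of the score she did give, whereas the analysis takes the difference between the two. The within-person correlation is lost for exactly those participants, and their imputed differences are too variable.

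At stake is precision of the primary contrast. The five extra participants were added to protect 80% power, and an imputation model that adds noise can use up part of that margin. A second possible cost is bias. If the chance of dropping out depends on the first-period score, the missing-at-random assumption needs that score in the model.

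**Working it through.** **Reproducing the plan's figures.** Read 27.8 as the SD of within-person differences and use the two-sided normal approximation n = ((1.960 + 0.842) × SD / difference)².
- Primary: (2.802 × 27.8 / 12.5)² = 38.8, so 39, as stated.
- FES-I, which "has a mean difference of 8.0, and standard deviation of 15.6": (2.802 × 15.6 / 8.0)² = 29.9, so 30, as stated.
- Attrition: 39 / 0.90 = 43.3, so 44, as stated.

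A two-sample formula with the same inputs gives 78 per arm and does not fit. The planned size therefore rests on paired differences.

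**What the stated model implies.** Let r be the correlation between periods and b the correlation of each period's score with baseline. The documents give neither, so both are assumptions here. With equal SDs in the two periods, a true pair has difference variance 2σ²(1 − r). A pair with one value imputed from baseline and order has 2σ²(1 − b²). The SD of an imputed difference is therefore 27.8 × √((1 − b²)/(1 − r)):

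| r | b = 0.2 | b = 0.5 |
|---|---|---|
| 0.3 | 32.6 | 28.8 |
| 0.5 | 38.5 | 34.0 |
| 0.7 | 49.7 | 44.0 |

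The excess over 27.8 grows with r and vanishes when r = b².

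**Effect on the trial.** AB/BA trials were simulated with 44 participants, difference 12.5, SD of differences 27.8 and 3,000 runs per setting. Week 12 was missing completely at random in 10%, about 4 women. Imputation was by normal regression with five imputed data sets, pooled by Rubin's rules with small-sample degrees of freedom. With no missing data, power is about 0.82 to 0.84.

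| r | b | Stated model: SE, power | Other period added: SE, power | Complete pairs: power | Loss, stated vs added (points) |
|---|---|---|---|---|---|
| 0.3 | 0.2 | 4.45, 0.755 | 4.37, 0.767 | 0.766 | 1.2 |
| 0.3 | 0.5 | 4.33, 0.799 | 4.32, 0.802 | 0.796 | 0.3 |
| 0.5 | 0.2 | 4.61, 0.760 | 4.39, 0.796 | 0.794 | 3.6 |
| 0.5 | 0.5 | 4.49, 0.775 | 4.38, 0.792 | 0.792 | 1.7 |
| 0.7 | 0.2 | 4.98, 0.689 | 4.41, 0.781 | 0.797 | 9.2 |
| 0.7 | 0.5 | 4.81, 0.708 | 4.43, 0.766 | 0.784 | 5.8 |

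Monte Carlo error is about √(0.75 × 0.25 / 3000) = 0.8 points for each power. A separately written simulation at b = 0.2 gives 0.781 vs 0.789 (r 0.3), 0.737 vs 0.776 (r 0.5) and 0.655 vs 0.757 (r 0.7), which are losses of 0.8, 3.9 and 10.2 points. At r = 0 there is no loss (0.806 vs 0.801). Interval width follows the SE: 4.61 / 4.39 is 5% wider at r 0.5, b 0.2.

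**How plausible is r = 0.7?** The single-period SD is 27.8 / √(2(1 − r)): 23.5 at r 0.3, 27.8 at r 0.5 and 35.9 at r 0.7. A score spread uniformly over 0 to 100 has SD 100/√12 = 28.9. An average of several 0–100 items with SD near 36 is unlikely, so the upper rows are an outer bound.

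**Bias, as illustration only.** In a constructed extreme case, dropout followed a low first-period score and fell almost wholly in one sequence. The stated model then estimated 12.9, 13.8 and 14.9 at r 0.3, 0.5 and 0.7 against a true 12.5. Adding the other-period score gave 12.4 to 12.5.

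**The case against.** The strongest reply is that little is at stake. About 4 of 44 women are affected and about 40 pairs stay intact, so it would be wrong to infer that the crossover as a whole loses its within-person correlation. Sections 2.2 and 2.14 also call the outcomes specific to the shoe or intervention, which gives no reason to expect a high correlation between two dissimilar shoes. This stands, and it is why the larger losses are not the expected ones.

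A second reply is that the list is not called exhaustive. In chained imputation incomplete variables can predict each other while a short sentence names only the complete predictors. That is possible but not the plain reading: the article chose to name the predictors, so what it names can be judged.

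Three stronger readings are tempting and lack support:
- **Week 6 score as the main driver of dropout, so the estimate will be biased.** The limitations in the Discussion say only that disliking either shoe's design may deter adherence. Nothing describes who drops out, and missingness completely at random produced no bias in the simulations.
- **Baseline MOSQ cannot concern a study shoe.** Section 2.5 places baseline before allocation of order, but section 2.3 has both pairs ordered before baseline. The documents do not say which shoe is rated, so b could be low or moderate; hence the two values used.
- **Five imputations are too few.** The text does not settle whether five counts imputations or chain iterations, and the number matters little beside the choice of predictors.

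Finally, the change cannot help women missing both periods.

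**Conclusion.** The point holds as a modest, avoidable loss of efficiency. The stated predictors do not match a paired design and analysis, and the direction is consistent across simulations. At 10% missing week 12 scores the power cost is about 0 to 4 points for between-period correlations up to 0.5 and about 6 to 10 points at 0.7. It is negligible at low correlation, or whenever r is close to b². From 0.5 upward the planned imputation gains nothing over complete pairs and mostly does worse, which defeats its purpose.

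The size rests on assumed values of r (0.3 to 0.7) and b (0.2 to 0.5), equal SDs in the two periods, all attrition falling on week 12, and five read as the number of imputed data sets. Bias is a possibility only, conditional on a dropout mechanism the documents do not describe.

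**What to change.** In section 2.14, state that imputation is done with one row per participant, so that week 6 and week 12 scores of the same outcome predict each other alongside baseline and order. Alternatively, make the primary analysis a likelihood-based mixed model fitted to all observed periods and keep imputation as a sensitivity analysis. The same wording should cover the secondary outcomes, for which the effect was not computed here. Say whether five is the number of imputed data sets or of chain iterations, and give the other number too. If the full plan already lets the two periods predict each other, one clause saying so closes the point.

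The cost is a sentence or two and negligible analysis work. It needs no change to recruitment or data collection.

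### The imputation size is set at five, which is valid but low: if it means five imputed data sets, a borderline primary p-value can cross 0.05 with the random seed

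*Protocol article*

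**What the plan says.** Section 2.14 (Statistical Analysis) of the protocol article gives the missing-data method in one sentence: "Multiple imputation will be used to replace any missing data using 5 iterations, with baseline scores and order as predictors". The same section states that "Analysis will adhere to the intention‐to‐treat principle for all randomised participants" and that "Analysis will be performed using a repeated measures analysis of variance". It gives no other number for the imputation.

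Section 2.13 (Sample Size) expects some loss: "To account for an estimated 10% attrition rate, we will recruit an additional 5 participants". The primary calculation uses "a mean difference of 12.5, standard deviation of 27.8, power of 0.80 and alpha level of 0.05".

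**The concern.** The one number given is open to two readings. In multiple imputation, iterations are the cycles that the algorithm runs before a completed data set is drawn. The number of imputed data sets is a separate setting. If the sentence means data sets, there are five. If it means cycles, the number of data sets is not fixed. The first reading is the more natural one, because a reader expects the size of a multiple imputation to be the number of data sets.

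All randomised women are to be analysed and about 10% are expected to be lost, so imputed values will enter the primary comparison. Pooled results from a few imputed data sets carry simulation noise that depends on the seed. If that noise is not small beside the distance between the observed result and the 0.05 boundary, the same 44 women could yield a significant result under one seed and a non-significant result under another.

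**Working it through.** **Inputs from the document.** Difference 12.5, SD 27.8, power 0.80, alpha 0.05, 39 women before attrition and 44 recruited (section 2.13); two-period AB/BA crossover (section 2.2); imputation from baseline scores and order, set at five (section 2.14).

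**Inputs assumed.** Two-sided alpha; 22 women per order; 27.8 read as the SD of the within-woman difference; between-period correlation 0.3 to 0.7; baseline-outcome correlation 0.3; five period-2 scores missing completely at random.

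**Step 1: reproduce the plan's figures.** n = ((1.960 + 0.842) × 27.8 / 12.5)² = 38.8, so 39. For the FES-I, ((1.960 + 0.842) × 15.6 / 8.0)² = 29.8, so 30. With attrition, 39 / 0.9 = 43.3, so 44. All three match. This supports the reading of 27.8 and a two-sided alpha.

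**Step 2: efficiency with five data sets.** In simulation of this design, the fraction of missing information (FMI) is 0.086, 0.099 and 0.149 at between-period correlations 0.3, 0.5 and 0.7. Relative efficiency is 1 / (1 + FMI/m):
- FMI 0.086, m = 5: 1 / 1.0172 = 0.983
- FMI 0.149, m = 5: 1 / 1.0298 = 0.971

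The estimate loses only 2-3% in efficiency.

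**Step 3: seed noise in the test statistic, by hand.** The seed-to-seed SD of t that comes from the estimate alone is about √(FMI/m). For m = 5 it runs from √(0.086/5) = 0.13 to √(0.149/5) = 0.17. For m = 50 it runs from 0.04 to 0.05. On 42 degrees of freedom, p = 0.04 corresponds to t = 2.12 and p = 0.05 to t = 2.02, a gap of 0.10. With five data sets the noise exceeds the gap; with 50 it is about half of it. The hand figure is a lower bound, because the pooled standard error and degrees of freedom also vary with the seed. The simulations give SDs of 0.15-0.24 with five and 0.045-0.07 with 50.

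**Step 4: simulated verdicts.** Each data set was imputed by Bayesian linear regression on baseline and order. The shoe contrast was pooled by Rubin's rules with small-sample degrees of freedom and compared with a pooling of several hundred imputations.

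| Situation | 5 data sets | 50 data sets |
|---|---|---|
| Near-exact p fixed at 0.04: share of seeds with p > 0.05 | 29-38% | 2-7% |
| Near-exact p between 0.02 and 0.10: verdict changes | about 17-26% | about 4-7% |
| All trials at a true difference of 12.5: verdict changes | about 4-9% | about 1-2% |

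At a true difference of 12.5, about 20-26% of simulated trials fall in the 0.02 to 0.10 band. With no true difference, the verdict changes in only about 1% of trials with five data sets.

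**Step 5: sensitivity to the amount missing.** With near-exact p = 0.04 and five data sets, the share of seeds above 0.05 is 17-24% with two scores missing and 39-45% with nine missing.

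**Step 6: pooling.** With two shoes and two orders, each effect in the planned ANOVA has one numerator degree of freedom, so F = t². The shoe difference and its standard error come from that model and pool directly by Rubin's rules.

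**The case against.** Four points can be made for the plan.

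1. *Five imputations are valid.* Rubin's rules inflate the variance by (1 + 1/m) and reduce the degrees of freedom, so inference already allows for a small m. This stands. The issue is reproducibility of a borderline verdict, not bias or a wrong error rate. A seed-to-seed SD in t of about 0.2 is also small beside its sampling SD of about 1.

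2. *The conditional rates look worse than the whole picture.* The 17-26% applies only to results already near 0.05. This stands, which is why the rate over all trials at the planned difference is given as well.

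3. *An unstated number of data sets may be left to the analysis plan.* This would hold if the sentence meant algorithm cycles only. But the article chose to state a size, and on its likely meaning that size is low. On either reading the sentence needs the same correction.

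4. *Fifty is a convention.* This also stands. Some seed dependence remains at 50, so the seed should be recorded as well.

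A reader might also infer that F statistics from the repeated measures ANOVA cannot be pooled, so that the stated analysis has no combined primary result. The document does not support that. It does not say that F values will be averaged, each effect has one degree of freedom, and the contrast with its standard error pools in the ordinary way. Naming the pooling rule is detail that an article commonly leaves to the analysis plan.

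**Conclusion.** The point holds as a free improvement of low to moderate priority. Read as five imputed data sets, the setting gives valid inference at about 97-98% efficiency, but it leaves avoidable seed dependence in the primary verdict. Roughly 17-26% of seeds change the verdict when the near-exact p is 0.02 to 0.10, and roughly 4-9% do so over all trials at the planned difference. With 50 data sets these fall to about 4-7% and 1-2%.

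The figures rest on the assumed correlations, on data missing completely at random and on five missing period-2 scores. They are approximate, being based on a few hundred simulated data sets or fewer per scenario. Fewer missing scores shrink the problem, and with no missing data it disappears. It would be wrong to infer that the primary result as such hangs on the seed: a clear result in either direction is unaffected.

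**What to change.** In section 2.14, replace the reference to five iterations with: at least 50 imputed data sets, with the number of algorithm iterations set separately and the random seed recorded. Add that the primary result is the shoe difference with its standard error, pooled by Rubin's rules with small-sample degrees of freedom. This contrast can come from the planned ANOVA or, equivalently, from a regression of the within-woman period difference on order. A mixed model is optional.

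The cost is two sentences and a few minutes of computing, with no extra data and no burden on participants. Recruitment has begun and results are expected in December 2026, so the change should be made and dated before analysis starts.
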